### Interim Analysis

Interim analysis of the study is planned according to the alpha spending rule. The p-values are constructed to maintain the overall study power of 80% with alpha level of 0.05, two-sided. The interim analysis is planned to be conducted at end of approximately 12 -18 months, depending on enrollment. This analysis will focus on controlling type I error (alpha). We will use group sequential design with Pocock’s approach. If we repeat the significance tests at a fixed level, it will increase the probability of obtaining a significant result under the null hypothesis. In other words, it will increase the error rate. Thus, the goal is to conduct these repeated significance tests while maintaining corresponding error rate. Pocock applied the repeated significance tests to group sequential trials with equally spaced information levels and derives a constant critical value on the standardized normal *Z* scale across different analytic stages that maintains the Type I error probability level. For example, with a significance level 0.05 in a two-sided test, the derived critical value at one stage is 2.413 on the standardized normal *Z* scale, which is larger than the fixed-sample critical value 1.96. The corresponding nominal *p*-value is 0.0158, which is smaller than the fixed-sample *p*-value 0.025. Sequential design will be carried out in SAS using PROC SEQDESIGN.

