**AND**

- Medically stable **AND** able to start intervention between 34-48 weeks PMA.

*Exclusion criteria:*

(related to inability to complete intervention, sensor placement, or clinic assessments)

- open wounds, skin condition precluding sensor placement
- immune deficiencies requiring protective isolation
- limb reduction defects
- Followed primarily in another clinic (including but not limited to meningomyelocele and related conditions/trisomy 21)
- bleeding disorders or ongoing need for anticoagulation
- palliative or hospice care (for life limiting conditions including, but not limited to trisomy 18, 13)
- known visual impairment at the time of enrollment
- DCFS custody
- No English-speaking caregivers
- Any other condition that would preclude participation in the study, as determined by the PI
- Previously enrolled in competing randomized trial with developmental outcome variables

Each child’s enrollment in the study will be approved by the child’s neonatologist.

Standard of care therapists

*Inclusion Criteria:*

- Therapist treating an infant enrolled in the study post-NICU, in either the standard of care group or the intervention group.

*Exclusion Criteria:*

- ​Not treating infant involved in the study

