# Qualifications to Conduct Research and Resources Available

We estimate that up to 75 children per year from Prentice NICU will be eligible to participate in the study (>60 per year with birth weights less than 1500 grams and approximately 15-20 per year meeting neurological inclusion criteria). We estimate that up to 35 children from Lurie NICU will be eligible to participate (approximately 20 per year with birth weights less than 1500 grams and approximately 25 per year meeting neurological inclusion criteria). We expect to recruit approximately 35-40% of these infants to meet our recruitment goals. We expect to recruit approximately 13 babies per year from UIC.

Time (Calendar months) devoted to conducting and completing this research by Key Personnel:

PI: [name], MD, Yrs. 1-3: 2.4; Yrs. 4-5: 1.2; Yr. 6:0.6

Co-I [name], Yrs. 1-6, 0.6

Co-I: [name], PT, PhD, Yrs. 1-3: 3; Yrs. 4-6: 0.96

Co-I: [name], Yrs. 1-3: 1.44; Yr. 4: 0.6; Yrs. 5-6: 0.36

Co-I [name], Yrs. 1-3: 2.4; Yrs. 4-5: 1.2; Yr. 6:0.6

Co-I [name], PT, MBA, Yr. 1: 1.8; Yrs. 2-5: 1.2; Yr. 6: 0.6

Co-I [name], Yrs. 1-3: 3; Yrs. 4-6: 6

Co-I [name], Yrs. 1-6: 0.6

Co-I [name], Yrs. 1-6: 0.6

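### The interim at about 12-18 months falls when at most about 19% of the primary-outcome information can exist, which does not fit the equally spaced Pocock boundary the protocol describes

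*Protocol*

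**What the plan says.** All of the interim design is in the Interim Analysis section of the Protocol. On timing: "The interim analysis is planned to be conducted at end of approximately 12 -18 months, depending on enrollment". On method it opens with "Interim analysis of the study is planned according to the alpha spending rule", then says "We will use group sequential design with Pocock’s approach" and explains that "Pocock applied the repeated significance tests to group sequential trials with equally spaced information levels". The only boundary value printed is introduced as an example: "the derived critical value at one stage is 2.413 on the standardized normal" scale, with nominal p 0.0158. The operating target is "overall study power of 80% with alpha level of 0.05, two-sided".

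The section refers to one interim. It gives no number of looks, no information fraction, no count of infants with the primary outcome, no named spending function and no starting point for the 12-18 month clock.

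Three other sections determine how much information the look would hold. The inclusion criteria require infants to be "able to start intervention between 34-48 weeks PMA". The Power Analysis asks for 77 evaluable infants per arm (154 in all) and plans for 20% or 30% attrition. Qualifications to Conduct Research and Resources Available estimates up to 75 eligible infants a year at Prentice and 35 at Lurie, says "We expect to recruit approximately 35-40% of these infants to meet our recruitment goals", and adds about 13 a year from UIC.

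**The concern.** An infant contributes to the primary comparison only on reaching 12 months corrected age, about 10 to 13 months after entry. A look 12-18 months into recruitment can therefore use only infants enrolled in roughly the first two to eight months, if any. The protocol ties the look to a calendar window and to enrolment, neither of which measures how many 12-month scores exist.

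Two things are at stake. First, the look spends alpha, or final power, on a comparison that can hardly support a stopping decision; if the boundary were crossed, the estimate would be far above the planned effect. Second, the timing conflicts with the equal-spacing condition that the same section gives for its boundary. The multi-site section adds to the first point: interim results are to be shared with the sites at PI meetings, where decisions on continuing are also taken, while most infants are still to be enrolled.

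**Working it through.** **Reproducing the plan's own figures.** A two-sample t-test with 77 per arm, an 8-point difference and two-sided alpha 0.05 gives power 90.8% at SD 15 (stated 90.1%) and 80.5% at SD 17.5 (stated 79.4%). Attrition: 154/0.70 = 220 (stated 220); 154/0.80 = 192.5 (stated 192). These agree closely enough to use 154 as full information.

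**Accrual.** (75 + 35) × 0.35 + 13 = 51.5 a year; (75 + 35) × 0.40 + 13 = 57 a year.

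**Lag from entry to outcome.** 12 months minus (PMA at entry − 40 weeks): 13.38 months for entry at 34 weeks, 12.00 at 40 weeks, 10.16 at 48 weeks.

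**Evaluable infants at month m** = (rate/12) × (m − lag) × (1 − attrition), or zero if m is below the lag; divide by 154 for information. The clock is assumed to start at first enrolment, with full accrual from then on.

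| Look | Low: 51.5/yr, 34 wk, 30% attrition | Entry at 40 wk, both rates, 20-30% attrition | High: 57/yr, 48 wk, 20% attrition |
|---|---|---|---|
| Month 12 | 0 (0%) | 0 (0%) | 7.0 (4.5%) |
| Month 15 | 4.9 (3.2%) | 9.0-11.4 (5.9-7.4%) | 18.4 (11.9%) |
| Month 18 | 13.9 (9.0%) | 18.0-22.8 (11.7-14.8%) | 29.8 (19.3%) |

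For example, the high corner at month 18 is 57/12 × (18 − 10.16) × 0.80 = 29.8, and 29.8/154 = 19.3%.

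**When half information arrives.** Month = lag + 12 × 77/(rate × retention). Earliest: 10.16 + 12 × 77/(57 × 0.80) = 30.4. Latest: 13.38 + 12 × 77/(51.5 × 0.70) = 39.0. The 20% point (31 infants) falls at months 18.3-23.6.

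**Pocock constants** for two-sided 0.05 with equal spacing, by numerical integration: 2.178 for two looks (nominal p 0.0294), 2.289 for three, 2.361 for four, 2.413 for five (nominal p 0.0158). The printed 2.413 is thus the five-look constant, whose first look belongs at 20% information. One interim plus a final is two looks, with the first at 50%.

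**Chance of crossing under the planned effect.** The expected Z at full information is 8/(15 × √(2/77)) = 3.31; at fraction t it is 3.31 × √t.

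- t = 0.10: expected Z 1.05; crossing probability 13% at 2.178 and 9% at 2.413.
- t = 0.19: 23% at 2.178 and 17% at 2.413.
- t = 0.50: 56% at 2.178 and 47% at 2.413.

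**Observed difference needed to cross** = c × 15 × √(4/n), n being total evaluable. With n = 30: 11.9 points (2.178) or 13.2 (2.413). With n = 20: 14.6 or 16.2. With n = 14: 17.5 or 19.3. The month-18 range is therefore about 12-19 points against the planned 8.

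**Overall type I error and power**, two looks with the first at 2-19% information and the same constant at both:

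| Constant | Overall alpha | Power, SD 15 | Power, SD 17.5 |
|---|---|---|---|
| 2.178 | 5.5-5.8% | 87.5-87.9% | 75.3-75.9% |
| 2.413 | 3.0-3.1% | 81.8-82.3% | 67.0-67.7% |

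On the same normal approximation a single test at 0.05 has power 91.1% at SD 15 and 81.0% at SD 17.5.

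**The case against.** The strongest reply is that the section names an alpha spending rule, and a spending function handles unequal spacing. That is right as far as it goes. A Pocock-type spending function at 13% information gives bounds of about 2.57 and 2.04, holds alpha at 5%, and leaves overall power at about 90.0% against 91.1%. But no function is named, the text goes on to describe a constant critical value, and no spending function can supply outcome data that do not yet exist.

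The second reply is that the window is approximate and depends on enrolment. It is flexible, but months 30-39 cannot be read as approximately 12-18, and enrolment does not count outcomes.

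Three stronger readings are tempting, and the document does not support them.

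- A reader might infer that hardly any infant has the outcome anywhere in the window. That fits month 12; at month 18 there could be 14-30.
- A reader might infer a serious loss of type I error control. The excess is 0.5-0.8 percentage points, and only with 2.178, which the protocol never prints. The printed 2.413 at two looks is conservative.
- A reader might infer that the protocol commits itself to a look at 50%. The number of looks is unstated; 50% follows only from taking the single interim literally, and five looks would call for 20% first.

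None of these qualifications makes the look informative. With 20-30% attrition, month 18 stays just short of 20% even in the most favourable corner.

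**Conclusion.** The timing is wrong as written. In the stated window the efficacy look would rest on 0-5% of the information at month 12 and 9-19% at month 18, against 50% for the single interim described or 20% for the first look under the printed constant. The main harm is a look with little chance of stopping under the planned effect, which would overstate that effect if it did stop, and which still costs alpha or power. At SD 15 the power cost runs from about 1 point with a suitable spending function to about 9 points if 2.413 is used at both looks. The departure from the 5% level is real but modest, in a direction that depends on which constant is meant.

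The figures assume a clock starting at first enrolment, uniform accrual at the protocol's rate, entry spread over 34-48 weeks PMA, and 20-30% attrition. Full accrual from the first day favours the plan: the protocol starts with a pilot cohort of 6-10 infants, and a slower start would lower every information figure. With no attrition by the time of the look, month 18 would hold 12.9-24.2%, still far from half.

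**What to change.** Replace the calendar window with a trigger on infants who have a 12-month corrected-age Bayley-4 motor score: 77 of 154 if there is one interim. State the number of looks, name the spending function, and compute the boundary at the information fraction actually reached.

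If that comes too late to be useful, drop the efficacy look. Keep a pooled check of SD, accrual and attrition at 12-18 months, without comparing arms, and test once at 0.05.

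Either change is a matter of wording and adds no infants or data. The cost is that the interim comes later or is lost. At 77 evaluable infants, enrolment would stand at 77/retention + rate × lag/12, that is from 77/0.80 + 51.5 × 10.16/12 = 140 to 77/0.70 + 57 × 13.38/12 = 174, out of the 192-220 planned. An early stop would then save few enrolments, which is an argument for the second option.

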### Data Management:

All personal information and study documentation that can identify participants will be kept secure to protect their privacy. Data collected during the study and shared with others will be de-identified and reference participants only by an alphanumeric code. The “master list” linking personal information to the alphanumeric code will not be shared outside of the study team.

Data will be collected and stored in compliance with HIPAA requirements. All collected data will be de-identified, stored in locked cabinets at the SRAlab with access limited to research staff, stored on password-protected computers (electronic folders will be private with limited access as determined by the PI) or stored in REDCap.

Access to REDCap data will be limited to study staff members who need access to complete study requirements, including data analysis. Data Use Agreements between actively enrolling study sites will allow SRAlab staff access to de-identified data from Lurie, Prentice, and UIC. Videos used as part of the Activity Playbook will be stored on Vimeo Premier, which is password protected. Videos of study participants recorded for assessment or fidelity checking purposes will be stored on a secure, HIPAA-compliant web server. These videos will not be shared unless the caregiver provides permission as part of the consent process.

Intervention session videos for fidelity will be destroyed after review and evaluation. Assessment session videos for fidelity will be kept until the end of the study and then destroyed.

Videos taken during sensor assessments and electronic data from sensors will be stored on a SRAlab secure research server and/or HIPPA-compliant Amazon Web Services platform.

Parent-reported data and forms completed by therapists will be entered into REDCap, a web-based data collection tool, which is supported by SRAlab. Neurodevelopmental assessment scores and comments, as well as but not limited to date of birth, expected delivery date, demographic information, and presence of risk factors, will also be stored in REDCap.

De-identified data will be stored indefinitely.

Data Quality Control:

Data collection will be reviewed by the study PIs and by the data safety monitoring board on a quarterly basis. Quality will be assessed based on completion of required study/assessment visits, completion of all necessary forms and their upload into REDCap, and collection of sensor data, if required. Data quality will be monitored through the use of data error/missing data reports through REDCap as well as specially developed quality control programs in R. Data entry double checks and fidelity monitoring may also be completed.

# Provisions to Monitor the Data to Ensure the Safety of Participants

Because this study Is a non-significant risk study, we will not require a DSMB.

# Provisions to Protect the Privacy Interests of Participants

Participants will be assigned unique study ID number when then are enrolled in the study, and all study data collected from that participant will be stored under that identifier. No identifying data will be stored with study data. The master key linking participants’ identities and study numbers will be stored separately under password protection and/or in locked cabinets, and will not be shared. Videos and photographs of study participants will not be shared without express written permission of the caregivers. Published results will use aggregate or de-identified data only.

# Compensation for Research-Related Injury

We will not provide any compensation for research related injuries.

# Economic Burden to Participants

We do not anticipate any significant economic burden to participants. Participants in the intervention group will receive the intervention in their home, at no charge. If participants do request in-clinic visits for the intervention, any parking expenses will be reimbursed. All participants will be reimbursed for each assessment time-point. They may also be provided with a parking voucher. Participants, or their insurance carrier, will be charged for non-study-related interventions or physician time during assessment visits. They will not be charged for any study-related developmental testing required as part of study assessments. For a typical visit to the Early Childhood Clinic, this will involve only the physician visits as the therapy assessments for the study are typical of what is normally done at a clinic visit. On rare occasions, a child may need an extra therapy assessment that is not part of the study (For example, the child may need to see a speech therapist in addition to the typical occupational therapy and physical therapy visits). They will not be charged for any study-related developmental testing required as part of study assessments. For participants who do not have access to necessary technology (e.g., smartphone, tablet, or computer) with which to watch videos, and who would otherwise qualify for the study and wish to participate, we may provide necessary resources to enable their participation, at the discretion of the PI.

# Consent Process

Consent will be required from the caregivers of the infant. Consent will take place while the infant is in the NICU or after discharge and may be completed in person, via telehealth, or telephone. Infants will be identified as potential participants in the study at approximately 33-34-weeks post-menstrual age (PMA) and may be consented up to approximately 48 weeks PMA.

# Non-English Speaking Participants

At least one of the infant’s caregivers (preferably the main caregiver) must speak and understand English, as the therapist(s) will need to be able to communicate effectively with the participant’s caregivers to provide the intervention, engage the caregiver(s), and document any barriers to implementation of the intervention or adverse events. In addition, caregivers will need to use Activity Playbook materials, which will be written/narrated in English, in order to provide the intervention. An inability of any caregiver to speak English is one of the listed exclusion criteria.

# Waiver or Alteration of Consent Process

No waivers of the consent process will be required. Because of the infant participants are under the age of 18, their consent is not required, and because of their age, their assent cannot be obtained. Consent will be obtained from biologic or adoptive parents or an individual legally authorized to consent on behalf of the child to general medical care.

***Process to Document Consent in Writing***

Parental permission will be obtained from one parent even if the other parent is alive, known, competent, reasonably available, and shares legal responsibility for the care and custody of the child.

Screening of potential study participants, those who decline, and those who consented and enrolled in the study, as well as a description of how consent was obtained, will be documented in EPIC. Study participants will be flagged in EPIC. Consent forms will be stored at the infant’s enrollment site, in REDCap, and in Study Tracker (as applicable).

*Setting:*

Participants will be recruited in the NICU at Lurie, Prentice, or UIC. Study staff will approach potential participants once the infant is medically stable, after obtaining permission from the child’s attending neonatologist. The research, which comprises a physical therapy intervention, will be conducted in the NICU until discharge, and then continued in the infant’s home. Assessments will be conducted in the clinic associated with the infant’s recruitment site. If necessary, intervention sessions or assessment sessions can be conducted at the infant’s home, or at another clinic site, depending on the participating family’s schedule or preference.

*Study Coordination:*

Study coordination will be performed by a Logistics & Management core, comprising site PIs from all participating study sites and the project PI, along with support staff from SRAlab. This core will provide the administrative, clinical, and technical expertise and leadership in the design and coordination, and implementation of this multi-site clinical trial. This core, led by the study PI, will be responsible for study monitoring at all sites and for coordinating participant recruitment, screening, enrollment and retention, for data and safety monitoring, data collection and analysis, adherence to the protocol-directed procedures and guidelines, and the prompt review, reporting and resolution of adverse events. External consultants will assist with protocol development and review study documents, but will not have access to any information on study participants.

### *Lead Coordinating Center*

SRAlab will provide the administrative and technical support for the study, and will coordinate subject recruitment, intervention delivery, and data collection across participating sites.

*Data Coordinating Center:*

SRAlab will act as the data coordinating center. We will establish Data Sharing Agreements with Lurie, Prentice, and UIC to enable access to their data as part of the study.

# Protected Health Information (PHI and HIPAA)

The research will involve collection of protected health information, including but not limited to participants’ name, birth date, parental information, NICU admission and discharge dates, address, information from infant and maternal medical records, and photographic/video images; caregiver’s telephone number, photographic/video images, and social security number (to enable study reimbursements). Language informing participants of the collection of this data and who may have access to it, as required by HIPAA. will be included on the consent form.

# Qualifications to Conduct Research and Resources Available

We estimate that up to 75 children per year from Prentice NICU will be eligible to participate in the study (>60 per year with birth weights less than 1500 grams and approximately 15-20 per year meeting neurological inclusion criteria). We estimate that up to 35 children from Lurie NICU will be eligible to participate (approximately 20 per year with birth weights less than 1500 grams and approximately 25 per year meeting neurological inclusion criteria). We expect to recruit approximately 35-40% of these infants to meet our recruitment goals. We expect to recruit approximately 13 babies per year from UIC.

Time (Calendar months) devoted to conducting and completing this research by Key Personnel:

PI: [name], MD, Yrs. 1-3: 2.4; Yrs. 4-5: 1.2; Yr. 6:0.6

Co-I [name], Yrs. 1-6, 0.6

Co-I: [name], PT, PhD, Yrs. 1-3: 3; Yrs. 4-6: 0.96

Co-I: [name], Yrs. 1-3: 1.44; Yr. 4: 0.6; Yrs. 5-6: 0.36

Co-I [name], Yrs. 1-3: 2.4; Yrs. 4-5: 1.2; Yr. 6:0.6

Co-I [name], PT, MBA, Yr. 1: 1.8; Yrs. 2-5: 1.2; Yr. 6: 0.6

Co-I [name], Yrs. 1-3: 3; Yrs. 4-6: 6

Co-I [name], Yrs. 1-6: 0.6

Co-I [name], Yrs. 1-6: 0.6

# multi-site research

Although not required by the Sponsor, we will establish a single-IRB for this study, with Lurie as the reviewing IRB (IRB of record) and UIC and NU(Prentice/SRAlab) as relying IRBs. We anticipate that the onboarding process for participating sites will occur concurrently with IRB review.

- No activities will occur at external sites until local IRB review is pursued or reliance agreements are fully executed.
- Any external site sign-offs or permissions will be acquired by external study teams in accordance with their local policies.
- IRB approval letters from external sites, documentation that IRB review at external sites is unnecessary, or fully executed reliance agreements will be provided when available with accompanying protocol updates.
- Non-compliance with the study protocol or applicable requirements will be reported in accordance with local policy

Potential subjects will be recruited at Lurie, Prentice, and UIC NICUs, and will be identified based on their medical history and examination including appropriate imaging. We will create flyers for distribution in the antenatal clinics and NICUs at participating sites (see attached documents).

Communication between sites will be accomplished by regular meetings of PIs, members of the logistics and management core, and project coordinators at each site. All sites will be provided with a copy of the current approved study protocol, consent document, and HIPAA authorization after each modification or revision, and all necessary approvals for each revision and continuing review will be obtained for each site before any changes are implemented.

All data will be maintained in REDCap, and data use agreements will be in place at each actively enrolling site to only allow access to data from that site. Data will be accessed by designated study staff at SRAlab, which is the data coordinating site for the study. Any necessary transmission of data will be achieved through HIPAA-approved email or cloud services. All participating sites will ensure confidentiality of personal health information and safety of data storage and transmission according to their individual institutional protocols, as required by the respective IRBs of record and state and Federal regulations and laws. Any and all instances of non-compliance with study protocols will be reported as required by respective institutional policies.

As the data coordinating center, SRAlab will be responsible for monitoring data fidelity, and will generate reports on a regular basis that will be shared with participating sites and reviewed at PI meetings to ensure data accuracy and completeness. SRAlab will also monitor adverse events and ensure all reporting requirements are met across sites. Meetings between PIs will be convened to address problems with study recruitment, and intervention implementation, and adverse events.

Interim results will be communicated with each site at PI meetings. Decisions on continuing of stopping the study will be made at each scheduled meeting or at additional meetings convened as necessary to address study findings or adverse events.

Data will be stored on REDCap indefinitely, and de-identified data as well as data analysis results will be provided to each site and made available to other investigators with necessary safeguards to ensure privacy of participants.

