### Randomization:

Participants (including those in the pilot study) will be randomized to the two treatment arms using the method of permuted blocks. Randomization sequences will be generated by a statistician, and will be uploaded into the REDCap randomization module. Randomization will be stratified by study site and by risk of neuromotor delay (mild vs. moderate/severe). Siblings in multiple births will be assigned to the same group, and outcomes assessed only for the infant with the most severe risk. In order to ensure unbiased evaluations, assessments of motor function and other outcomes will be performed by different study team members than those administering treatment, and although this is not a blinded study, therapists conducting study evaluations will be blinded to treatment arm assignment whenever possible.

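### Interim results go to every site and stopping is open at any PI meeting, with efficacy stopping not confined to the formal interim and conflicting statements on a DSMB

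*Protocol*

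**What the plan says.** Access and decisions (Protocol, multi-site research). Results are shared: "Interim results will be communicated with each site at PI meetings". Stopping is then addressed: "Decisions on continuing of stopping the study will be made at each scheduled meeting or at additional meetings convened as necessary to address study findings", with adverse events named as the other reason for an extra meeting. On who meets, the section says: "Communication between sites will be accomplished by regular meetings of PIs, members of the logistics and management core, and project coordinators at each site".

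Oversight. Under Study Coordination, the Logistics & Management core consists of the site PIs and the project PI with support staff, and "This core, led by the study PI, will be responsible for study monitoring at all sites". Its duties also cover recruitment, retention, data and safety monitoring, and analysis. External consultants are given no participant information. Data Quality Control (under Data Management) states: "Data collection will be reviewed by the study PIs and by the data safety monitoring board on a quarterly basis". The section that follows it, Provisions to Monitor the Data to Ensure the Safety of Participants, states: "we will not require a DSMB".

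Blinding (Randomization, in the Data Analysis Plan): "although this is not a blinded study, therapists conducting study evaluations will be blinded to treatment arm assignment whenever possible".

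Discretion (Withdrawal of Participants). The PI may withdraw infants for medical instability or poor compliance. Data already collected from a withdrawn infant stay in only if the researchers consider them scientifically relevant.

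The formal look (Interim Analysis). A Pocock group sequential test is planned at about 12 to 18 months, at overall two-sided alpha 0.05. The example critical value is 2.413, with nominal p 0.0158. The interim is described in the singular, and the total number of looks is not given.

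**The concern.** Two protections are missing, and the protocol's own wording rules them out as it stands.

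The first is a firewall. The only interim analysis the protocol describes is a between-arm significance test, so the natural reading of interim results is comparative. Those results go to people who can still influence the data: they recruit, work on retention, may withdraw infants, and decide whether a withdrawn infant's data count. With families and treating therapists aware of allocation, and assessor blinding not guaranteed for an examiner-administered outcome, knowledge of the emerging difference could shift any of these. Such bias cannot be removed in the analysis.

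The second is a limit on when efficacy can stop the trial. A group sequential boundary protects alpha only for the looks it was built for. The multi-site section lets study findings lead to a stopping decision at any meeting and does not tie efficacy stopping to the planned interim.

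The contradiction on the DSMB leaves it unclear whether any independent body exists to hold comparative results. An analysis plan cannot simply fill this in: a firewall written there would contradict what the protocol says about sharing results with the sites.

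**Working it through.** **1. The passages side by side**

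| Question | Statement | Section |
|---|---|---|
| Who sees interim results? | Every site | multi-site research |
| Who attends the meetings between sites? | PIs, core members, site coordinators | multi-site research |
| When can the trial be stopped? | Any scheduled or extra meeting, on study findings or adverse events | multi-site research |
| When is efficacy formally tested? | About 12 to 18 months; number of looks not given | Interim Analysis |
| Is there a DSMB? | Yes, it reviews data collection quarterly | Data Quality Control |
| Is there a DSMB? | No, not required | Provisions to Monitor the Data |

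Rows 1 to 3 put the results and the stopping decision with the trial team. Rows 3 and 4 do not limit efficacy stopping to the formal look. Rows 5 and 6 cannot both hold. No section restricts what the sites see to pooled data.

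**2. Reproducing the protocol's boundary figure**

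Inputs: two-sided overall alpha 0.05 and equally spaced looks (Interim Analysis). With K looks at information fractions t_k = k/K, the null model is a score process S with independent increments S(t_k) − S(t_{k−1}) ~ N(0, t_k − t_{k−1}), and Z_k = S(t_k)/√t_k. The type I error of a constant critical value c is

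α(c, K) = P(|Z_k| ≥ c for at least one k ≤ K),

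computed by recursive numerical integration. The Pocock constant solves α(c, K) = 0.05, and the nominal two-sided p is 2[1 − Φ(c)].

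| K (final included) | Pocock c | Nominal p | α(2.178, K) | α(2.413, K) |
|---|---|---|---|---|
| 2 | 2.178 | 0.0294 | 5.0% | 2.75% |
| 3 | 2.289 | 0.0221 | 6.55% | 3.66% |
| 4 | 2.361 | 0.0182 | 7.78% | 4.39% |
| 5 | 2.413 | 0.0158 | 8.80% | 5.00% |

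The protocol's pair reproduces: 2[1 − Φ(2.413)] = 0.0158. It is the constant for five looks. One interim plus the final analysis would use 2.178.

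**3. What the table shows**

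The protocol describes one interim and quotes a five-look constant, so the number of looks that the alpha rule covers is not settled. If 2.178 were adopted for one interim plus final, and efficacy were then tested at further meetings, the error would rise from 5.0% at two looks to 8.8% at five. If 2.413 were used and only two looks took place, the error would be 2.75%, which is conservative. The direction and size of any departure from 5% therefore depend on a number the protocol does not give.

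**The case against.** The strongest reply is that the multi-site section describes management meetings, not significance tests. The PI meetings are convened over recruitment, implementation and adverse events, and decisions on safety or feasibility spend no efficacy alpha. Nothing says outcomes are compared by arm at each meeting, and the words by arm do not appear beside interim results. That stands.

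A reader might infer unlimited efficacy looks and put a large figure on them: an unadjusted 1.96 at 5, 10 or 20 equally spaced looks gives 14.2%, 19.3% or 24.8%, and 2.413 gives 5.0%, 7.1% or 9.5%. The document does not support those as estimates:
- Interim Analysis itself warns against repeated testing at a fixed level and adopts Pocock.
- A quarterly interval could only come from the data-quality review, which concerns visits, forms and sensor data.
- The primary outcome arrives at 12 months corrected age, roughly a year after enrolment. Even over an assumed five years, about 4 of 20 quarterly meetings would have no primary data, and the rest would not be equally informative.

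A reader might also infer bias through the PIs' choice of risk stratum. That is weak. Neonatologists apply listed criteria, only the catch-all item is at the PI's discretion, and the stratum serves the randomization.

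Two safeguards deserve credit. Outcome assessors are different people from the treating therapists. Data use agreements limit each site to its own data, though this does not reach results presented at a joint meeting.

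None of this supplies a firewall, ties efficacy stopping to the formal interim, or resolves the DSMB contradiction.

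**Conclusion.** The point holds in this form: the protocol sends interim results to the site teams, leaves efficacy stopping unconfined to the formal interim, and contradicts itself on a DSMB. In a trial that is not blinded, with PI discretion over withdrawal and researcher discretion over keeping withdrawn infants' data, this is an avoidable route to operational bias and to stopping outside the alpha rule. It needs settling before the first interim, because disclosure cannot be undone.

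The conclusion rests on reading interim results as including the comparative test under Interim Analysis. That is the natural reading, since no other interim is described, but the term is not defined. Neither the operational bias nor the alpha inflation can be sized from the document. The 5.0% to 8.8% range (2.178, two to five equally spaced looks) is illustrative only. A claim that efficacy will be tested without limit goes further than the text.

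**What to change.** In multi-site research, replace the sharing of interim results with a statement that PIs and sites receive only pooled reports on data quality, recruitment and adverse events, plus a recommendation to continue or stop. State that between-arm outcome results are seen only by the statistician running the interim and by whichever monitoring body is confirmed.

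Reconcile Data Quality Control with Provisions to Monitor the Data on whether a DSMB exists. The fix should not presume the answer: the board mentioned is described only as reviewing data collection, so if it is kept, its remit must be extended to comparative results.

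In Interim Analysis, fix the number of looks and give the matching constant: 2.178 for one interim plus final, or 2.413 if five looks are intended. State that stopping for efficacy is considered only at those looks, while safety and feasibility decisions may be taken at any meeting.

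If no monitoring body is wanted, drop the efficacy interim, so that no comparative result exists before the end.

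Cost: mainly protocol wording. PIs do not see comparative results until the end. Keeping a board means a wider remit and restricted handling of the interim output, which is new work. Dropping the interim gives up the chance of stopping early for efficacy.
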